### Recruitment {15}

Participants will be recruited for the trial via flyers, word-of-mouth recommendation, and online advertisements in sources local to the Portland, OR metro area. Retention strategies include the use of stipends dispensed for clinical screening and each clinical visit completed following enrollment. The study aims to recruit a sample that is 50% male and 50% female in order to maximize the generalizability of our findings to both men and women.

## Assignment of interventions: allocation

### Sequence generation {16a}, concealment mechanism {16b}, implementation {16c}, blinding {17a}, and unblinding {17b}

Randomization will occur within 30 days of screening by blocking within the randomization sequence, with randomization stratified by biological sex. The initial randomization series will be generated using readily available electronic random sequence generators. The randomization “code” will be created by a staff member not involved in trial operations and kept in a sealed envelope with a signature across the label and dated the day of creation. This envelope will be kept in a dedicated study folder and locked in the office of the Research Integrity Officer or designee. Thirty-two opaque envelopes will be created, sequentially numbered include a designation of the code for the assigned intervention based on the randomization sequence, and signed across the seal. Masking of the interventions (i.e., xanthohumol or placebo) will be accomplished by engaging trained staff not involved in trial operations to label product bottles based on the randomization code. Product bottles will be stored in separate locked cabinets by code and maintained in a temperature-controlled environment, with temperature logged weekly to assess environmental stability. Upon confirmation of eligibility and consent, Study Coordinators will then open the next sequentially numbered envelope at the time of randomization, the envelope number will be recorded, and allocation (As “A” or “B”) disclosed to both participant and coordinator for the first time, and the corresponding product will be removed from its locker and dispensed in the bottle to the participant. Thus, the trial will be triple-masked without PIs, co-investigators, study coordinators, or participants knowing allocation assignment of study participants. Unmasking is permissible if the DSMB requires it upon review and in the case of a serious adverse event.

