### Adverse event reporting and harms {22}

Adverse event monitoring will occur using a standardized, multi-system, 81-item adverse event questionnaire based on the National Cancer Institute’s Common Terminology Criteria for Adverse Events. The adverse event questionnaire will be administered verbally by study staff at each of the clinical visits, including the initial screening visit, with a query to determine if other symptoms not elicited by the questionnaire have been experienced. Participants will be encouraged to contact study staff between study visits if they are experiencing any new, unusual, or bothersome symptoms. Adverse events reported between study visits (i.e., not reported on the 81-item adverse event interview during scheduled visits) will be termed a “spontaneous report” adverse event and will be documented within the participant’s file by the study staff to capture the severity/grade of the report, any clinical actions taken, and the current state of the adverse event. Following a spontaneous report, the study team, in coordination with a participant’s physician as needed, will develop a response or monitoring plan, which will also be documented.

All reported adverse events, as well as the length of duration, will be reported upon trial completion with a comparison of frequency between groups. Attributability to the intervention will be determined on a case-by-case basis by the clinical investigators and DSMB members according to accounts of the event(s) in previous research, whether the symptom was present at baseline, the severity and clinical trajectory of the symptom (i.e., did it worsen with accumulated exposure), whether similar symptoms accumulated in one group vs. another, and/or if the symptom was subjectively attributed to another cause *by the participant* (e.g., wrist pain following an injury at work).

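### Two shared product codes, A and B, mean that one code break known to site staff reveals every participant's treatment

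*Protocol article*

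**What the plan says.** The procedure is set out in the protocol article under Sequence generation {16a} to unblinding {17b}.

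- Randomization proceeds "by blocking within the randomization sequence, with randomization stratified by biological sex". The block size is not given.
- Masking relies on "engaging trained staff not involved in trial operations to label product bottles based on the randomization code". On storage the text says: "Product bottles will be stored in separate locked cabinets by code".
- At enrolment, "Study Coordinators will then open the next sequentially numbered envelope at the time of randomization". The result, A or B, is "disclosed to both participant and coordinator for the first time, and the corresponding product will be removed from its locker and dispensed".
- The code is held in one sealed envelope, locked in the office of the Research Integrity Officer or a designee.
- On code breaks: "Unmasking is permissible if the DSMB requires it upon review and in the case of a serious adverse event". The section does not say who receives the result.
- From these arrangements the section concludes that principal investigators, co-investigators, coordinators and participants do not know allocation.

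Under Adverse event reporting and harms {22}, study staff collect adverse events by verbal questionnaire. Clinical investigators and DSMB members judge attributability case by case. One of the factors they may weigh is "whether similar symptoms accumulated in one group vs. another".

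**The concern.** With only two codes, the whole allocation hangs on one unknown: whether A or B is xanthohumol. Coordinators see the letter of each participant as they open the envelopes. One answer to that question, for one participant, answers it for everyone. A code break cannot be confined to one person for anyone who holds the letters, however carefully the envelope is opened.

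Two further effects follow. Where letters repeat within blocks, the person opening envelopes can partly anticipate the next letter, and this becomes anticipation of treatment once the key is known. A letter shared by a whole arm also lets symptoms be sorted by arm without any formal unmasking.

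What is at stake is mainly adverse event reporting and attribution. Both belong to the primary safety and tolerability aim, and both involve judgement by participants and staff.

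**Working it through.** **Inputs.** Two codes, 32 envelopes, blocking and stratification by sex come from the randomization section. Enrolment of up to 16 per arm, 8 of each sex, comes from Sample size {14}.

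**The plan's own figure.** 12 per group with 25% attrition gives 12 / (1 − 0.25) = 16 per arm, and 2 × 16 = 32. This agrees with the 32 envelopes. Each sex stratum holds 8 + 8 = 16.

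**Step 1: reach of one code break.** Suppose one participant with letter A is found to be on xanthohumol. Then every A is xanthohumol and every B is placebo. For anyone holding the letters, 32 of 32 treatments are known at full enrolment. With a unique number per participant, the same event reveals 1 of 32 directly. The other numbers carry no repeated letter from which the rest can be read off.

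**Step 2: predictability of the next assignment.** Block size is not stated, so I assume sizes that divide 16. I also assume a guesser who knows the block size and all earlier letters in the stratum. For a block of 2m, always naming the letter with more places left:

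- expected correct guesses per block = m + (4^m / C(2m, m) − 1) / 2
- expected assignments known with certainty per block = 2m / (m + 1)

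For blocks of 4 (m = 2), correct guesses are 2 + (16/6 − 1)/2 = 2.83 of 4, and certain assignments are 4/3 = 1.33 of 4.

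| Assumed block size | Certain | Guessed correctly | Correct of 32 |
|---|---|---|---|
| 2 | 50% | 75% | 24.0 |
| 4 | 33% | 71% | 22.7 |
| 8 | 20% | 67% | 21.3 |
| 16 | 11% | 63% | 20.1 |

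Pure chance gives 50%, or 16 of 32. While the key is sealed, these figures describe prediction of the letter only. They describe prediction of treatment only for participants randomized after the key becomes known or is correctly inferred.

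**Step 3: who can pool information by letter.** Coordinators open the envelopes and see the letters. Under Provisions for post-trial care {30} the coordinator telephones participants about new adverse events. Under Plans for assessment and collection of outcomes {18a} the coordinator may export study data. Letter, symptoms and laboratory values can therefore meet in one pair of hands.

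**Step 4: attribution against masking.** The harms section lets clinical investigators weigh accumulation by group. Doing so requires events to be viewed by arm, at least as A against B. The randomization section says the investigators do not know allocation. The two can be squared only if investigators see letters but not treatments, or if someone else makes the group comparison. The article does not say which. Attributability also feeds the active-withdrawal rule under Criteria for discontinuing {11b, 21b}, so the answer has consequences.

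**The case against.** The masking has real strengths. Capsules are identical, xanthohumol is described as odorless, the key is sealed and locked away, and labelling is done by people outside trial operations. Unmasking is permitted, not automatic. A result kept within the DSMB would leave site staff masked, and handling rules may sit in the Data Safety and Monitoring Plan, which is not shown. No attributable serious adverse events are expected, apart from an unidentified allergy. All of this stands, and it makes the harmful event less likely. It does not change the reach of that event if site staff do learn a result. The two shared letters are a stated procedure, not a detail left to a fuller document.

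A reader might infer several stronger things that the documents do not support:

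- **Allocation is predictable from the start.** Earlier letters foretell the next letter, not the treatment. A coordinator who expects B without knowing what B is cannot steer participants towards either treatment. The percentages also rest on an assumed block size, which may properly be withheld; varying block sizes would lower them.
- **The coordinator conducts the adverse event interview.** The harms section says study staff. Overlap at a single site is plausible but not stated.
- **Staff will work out which letter is active.** No side-effect signature is described, and Sample size {14} says previous human studies have not suggested toxicity. Shared letters make inference easier, but nothing shows that it will happen.
- **The primary result is biased.** The primary outcome metric is mean laboratory change to week 8, measured by an outside laboratory, so observer bias has little purchase. PROMIS-29 is tertiary.
- **Attribution is openly unmasked.** Group accumulation is one of several factors, shared with DSMB members, and an A-against-B pattern does not by itself say which arm is active. This is a tension to resolve, not a demonstrated breach.

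**Conclusion.** The concern holds as a weakness in the masking design. If site staff learn one participant's treatment, those who hold the record of letters know all of them: up to 32, against 1 directly with unique numbers. This rests on two conditions: someone at the site learns the result, and that person holds or can obtain the letters. The text places no limit on the first, and the procedure supplies the second. The figure of 32 is the enrolment ceiling; an earlier break exposes those randomized so far and makes later blocked assignments partly predictable as treatments.

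Exposure is greatest for adverse events and their attribution and small for laboratory outcomes. It would go too far to say that the trial is unmasked as written or that its allocation is already predictable by treatment. This is an improvement worth making, not a fault that invalidates the design.

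**What to change.** Have the independent labelling staff already in place put a unique number on each participant's product. Show only that number in the envelope, store product by number, and keep the list linking number to treatment locked with the Research Integrity Officer or designee. Make each code break specific to one participant, and state who may receive the result.

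Apply this to participants not yet randomized. Those already holding a letter stay linked to one another, so for them the remaining protection is to restrict who learns any code-break result.

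Separately, reconcile the attribution paragraph in the harms section with the masking statement in the randomization section, for example by leaving the between-group comparison to the DSMB.

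The cost is relabelling, a numbered list of up to 32 entries and a short amendment. The number of bottles per participant is not given, so the relabelling effort cannot be stated exactly. Sample size and endpoints are unaffected.

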## Data collection, management, and analysis

### Plans for assessment and collection of outcomes {18a}

Each participant will be assigned a unique alpha-numeric ID upon screening. All blood and urine aliquot tubes, stool collection vials, and associated paperwork will be marked using the unique ID to protect participant confidentiality. All data resulting from study visits will be collected on standardized CRFs and through administered survey data. Data from CRFs will be transferred to a secure REDCap database, with survey entry entered directly, for data management and subsequent quality control checks [27]. Periodic data audits will be conducted monthly throughout the trial, and all data in REDCap will be confirmed from source documents prior to any analyses. All data will be kept for 3 years following completion of all grant activities. All source documents are identified only by an alphanumeric study ID and stored in a locked filing cabinet in a locked document storage room; all electronic data are stored on REDCap on a secure server requiring separate passwords to access the server and REDCap. REDCap user rights are carefully controlled to only allow the biostatistician, coordinator, and PI to export study data, all of which are de-identified.

### Plans to promote participant retention and complete follow-up {18b}

Retention will be promoted by a determined monetary compensation strategy with disbursement of funding after week 4 and week 8 clinical visits. For situations in which the participant is unable to complete an in-person clinical visit, protocol deviations will be followed on each case-by-case basis upon approval by the investigation team.

### Plans for collection, laboratory evaluation, and storage of biological specimens for genetic or molecular analysis in this trial/future use {33}

Blood-based specimens collected from study participants for clinical safety parameters will have an orchestrated same-day delivery to a Quest Diagnostics lab for analysis. Other blood-based samples for plasma analysis will be centrifuged at 2200–2500 rpm for at least 15 min prior to serial 500 μL aliquots to be stored in < − 70 °C at the study site. Urine specimen collected will be measured for overall collected volume, and serial 1 mL aliquots will be stored in < −70 °C at the study site. Stool specimens collected will be stored according to the specific requirements of the sample type: room temperature for microbial DNA analysis and < −70 °C for all other sample types at the study site. Samples stored at the study site will be labeled for identification using a format including study ID, visit number, and date collected until ready for analysis by partner sites upon which time transportation will be arranged to ensure sample integrity.

Study participants may indicate willingness for the study team to collect and store additional biological specimens at the baseline clinical visit and provide verbal confirmation at each subsequent clinical visit. These specimens will include up to four 1-mL vials each of urine and plasma for future analysis with respect to xanthohumol.

### Laboratory analysis outcomes {12}, statistical methods {20a, 20b, 20c}

Relevant laboratory-based safety measures were chosen as the primary safety outcomes, because this trial is intended to precede a clinical trial in adults with Crohn’s disease—a clinical population potentially vulnerable to anemia, liver toxicity, renal abnormalities, etc. Therefore, a formal assessment of laboratory changes in healthy humans provides critical information to guide expectations for changes in laboratory markers and associated adverse clinical effects in future research in Crohn’s and other clinical populations.

The primary objective’s laboratory-based outcome domains (and corresponding measures) are liver function (AST, ALT, alkaline phosphatase, bilirubin), renal function (BUN, creatinine, estimated glomerular filtration rate), hematology (red blood cell count, hematocrit, hemoglobin, white blood cell count), and electrolytes (sodium, potassium, calcium, chloride) measured every 2 weeks for 8 weeks. The primary outcome metric for comparison between study groups is the mean change from baseline to week 8. However, all parameters will be similarly evaluated at each follow-up time point, by formally comparing mean change from baseline to follow-up between groups. Comparisons at a single follow-up will use 2-sided independent *t* tests; omnibus tests for differing trends over time will employ linear mixed models with time point as a repeated factor and study group as an independent factor.

Primary outcome laboratory measures will be analyzed by first assessing descriptive statistics including mean, median, and standard deviation. All distributions will be tested for skew and transformed (e.g., natural log transformed) as needed to reduce the influence of skew in subsequent analyses. If inspection of distributions indicates significant non-normality that cannot be corrected with standard transformations, significance will instead be calculated using a non-parametric Wilcoxon signed rank test. The primary analysis will be a per-protocol analysis as this trial is a phase I trial focused on clinical toxicity, not a definitive efficacy or effectiveness trial; therefore, we are investigating the clinical and mechanistic effects of the product for those participants who took the experimental agent only. As a sensitivity analysis, missing laboratory data will be imputed by multiple imputation to assess the robustness of study results to imputation.

As an element of the evaluation for safety of the intervention, the percentage of laboratory newly abnormal (for values that were within the clinically normal range at baseline) per clinical laboratory reference ranges for each lab parameter will be reported at each time point and the percentage will be compared between groups by Fisher’s exact test. Assessment for changes in the distribution of each lab parameter will be performed by presenting means and confidence intervals (CI) for the change in each group, as well as the mean CI for the difference between groups; significance will be tested using 2-sided, unpaired *t* tests (or, if inspection of distributions indicates strong non-normality, with a non-parametric Wilcoxon signed rank test) of the mean values for the xanthohumol group compared to the placebo group. Assessment for overall *increases* or *decreases* in collected parameters will be tested for linear trends of the means by linear mixed ANOVA, considered significant if *p* < 0.05, with time point as a repeated factor. This may be suggestive of evidence for cumulative toxicity if trending in a clinically deleterious direction.

Health-related quality of life, measured by PROMIS-29, is included as a tertiary measure of gross changes in health. PROMIS-29 includes 7 validated subscales (physical function, anxiety, depression, pain intensity, pain interference, sleep, social interactions), each of which will be calculated as a mean by group, and means will be compared between xanthohumol and placebo, with the primary comparison being of mean changes from baseline to week 8. Significance of changes in QOL measures will be tested according to the same plan outlined for laboratory markers, above.

Given the small sample size of this clinical trial, changes in results related to the secondary objective including inflammatory cytokines, gut permeability biomarkers, and markers of endotoxemia are considered preliminary. Thus, our principal assessment for such exploratory outcomes will be of estimated effect sizes, calculated as a *Cohen’s d* statistic for difference between study groups, using change from baseline at each 2-week interval. The primary effect estimate will be for changes from baseline to week 8. We will also perform formal statistical comparisons with adjustments for skew as outlined in our primary objective analysis. The following will be considered evidence of possible effects for our secondary objective: (1) statistically significant effects for changes in cytokines of interest and/or (2) calculation of a Cohen’s *d* value for effect size estimation greater than 0.5 (with larger *d* indicating a larger potential effect size).

Finally, respective of our tertiary objective, we will identify and quantify xanthohumol and xanthohumol-derived metabolites in plasma, urine, and stool samples. The metabolite profile data will then be used for correlation with the time-resolved gut microbiome analysis. This approach will allow us to determine links between metabolite profiles, gut microbiome compositions, and proteomic data [29–36]. We will also quantify bile acids in plasma and stool samples as well as develop analytical methods for assessing microbiome compositional changes as appropriate to the study sample size [32, 37–49].

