## Hypotheses

We hypothesize that xanthohumol, at a dosage of 24 mg per day, will be safe and tolerable in trial participants as demonstrated by frequency of laboratory abnormalities or reported adverse events observed between groups not being significantly higher, and at most 50% higher in the intervention group. Additionally, we hypothesize xanthohumol and its microbiota-derived metabolites will reduce biomarkers of inflammation and modify barrier function in the inflamed gut. We anticipate xanthohumol will produce a specific microbiota-based biological mechanistic signature, which will provide the groundwork to determine its therapeutic potential in various chronic diseases.

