### Sample size {14}

A sample size of twenty-four (*n* = 12 per group) provides 80% power to detect a 50% difference in proportions of participants between groups by chi-squared test experiencing a laboratory abnormality or adverse event at a significance threshold of *α* = 0.05. To account for up to 25% attrition, up to 16 adults (8 biologically male and 8 biologically female participants) will be enrolled in each study arm. Given that this phase I trial is intended as a step toward a phase II clinical trial in Crohn’s disease, for which few effective treatments exist, the investigational drug is commonly available in the diet, and previous human studies have not suggested any toxicity, the present trial was powered to detect gross toxicity resulting in frequent adverse events and/or laboratory-measurable toxicity. However, interim halting criteria were also used to assess safety; an accumulated frequency of 25% reaching laboratory halting criteria was pre-specified as a criterion for halting the trial and requiring detailed review by the FDA, NCCIH, and IRB.

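### The primary laboratory metric (difference in mean change) does not match the proportion endpoint behind the hypothesis and the 80% power, and it is insensitive to severe injury in a minority

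*Protocol article*

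**What the plan says.** In the Protocol article, *Laboratory analysis outcomes {12}, statistical methods {20a, 20b, 20c}*, the laboratory domains are liver, renal, haematology and electrolytes, measured every 2 weeks for 8 weeks. "The primary outcome metric for comparison between study groups is the mean change from baseline to week 8". On the test: "Comparisons at a single follow-up will use 2-sided independent" (the t test). Skewed measures are to be "transformed (e.g., natural log transformed) as needed to reduce the influence of skew in subsequent analyses", and if that fails, "significance will instead be calculated using a non-parametric Wilcoxon signed rank test". On the analysis set: "The primary analysis will be a per-protocol analysis as this trial is a phase I trial focused on clinical toxicity".

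Two other sections frame the question as a count of people. *Hypotheses* defines safety through the "frequency of laboratory abnormalities or reported adverse events observed between groups". *Sample size {14}* says that the planned arm size of 12 "provides 80% power to detect a 50% difference in proportions of participants between groups by chi-squared test". A participant counts there through either an abnormal laboratory finding or an adverse event, alpha is 0.05, and the section describes the target as gross toxicity.

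A count comparison does exist. The same statistical section compares the percentage of newly abnormal values by Fisher's exact test, for each parameter at each time point, as one element of the safety evaluation. It is not the primary metric.

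**The concern.** The primary metric averages values over an arm, while the hypothesis and the sizing count affected participants. Two things follow.

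First, the power statement says nothing about the analysis that is labelled primary.

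Second, toxicity in a minority appears as a few very large values. In a two-sample t test these raise the SD along with the mean, so the statistic hardly grows. At stake is a primary result that reads as no significant change in a liver or renal marker while up to a quarter of the xanthohumol arm (3 of 12) has a large rise. This is the kind of harm that the sizing section says the trial was built to find.

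**Working it through.** **1. The plan's own figure.** Inputs from *Sample size {14}*: alpha 0.05, power 80%, 50-point difference, chi-squared test. Formula: n = [1.96·√(2p̄q̄) + 0.842·√(p₁q₁ + p₂q₂)]² / (p₂ − p₁)².
- 0% v 50%: [1.96·√0.375 + 0.842·√0.25]² / 0.25 = 10.5, so n = 11. Power at 12 is 0.856.
- 5% v 55%: [1.96·√0.42 + 0.842·√0.295]² / 0.25 = 11.9, so n = 12. Power at 12 is 0.802.
- 10% v 60%: n = 14. Power at 12 is 0.762.
- Attrition: 12 / (1 − 0.25) = 16.

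The stated 12 and 16 reproduce for an absolute 50-point difference with a control rate of about 0-5%. The calculation is for a proportion. Nothing in it concerns a mean or an SD.

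**2. Limit of the t statistic on raw change.** Let k of n treated participants rise by a very large M, with all other changes negligible. The mean difference is kM/n. The treated variance is M²k(n−k)/[n(n−1)]. With equal arms the pooled squared standard error is that variance divided by n. M cancels, leaving t → √[k(n−1)/(n−k)].

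| k | n = 12 (critical 2.074) | n = 16 (critical 2.042) |
|---|---|---|
| 1 | √(11/11) = 1.00, p = 0.33 | 1.00, p = 0.33 |
| 2 | √(22/10) = 1.48, p = 0.15 | 1.46, p = 0.15 |
| 3 | √(33/9) = 1.91, p = 0.069 | 1.86, p = 0.073 |
| 4 | √(44/8) = 2.35, p = 0.028 | 2.24, p = 0.033 |

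**3. Finite rises.** Assumptions (none is in the document): ALT median 20 U/L, between-person log-SD 0.35, log-SD 0.20 at each visit, 12 per arm, 8-fold rise in k xanthohumol participants, and all of them contributing a week 8 value. Simulated rejection rates at two-sided 0.05:

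| Affected | Raw change, t test | Log change, t test | Rank-sum |
|---|---|---|---|
| 0 of 12 | 5% | 5% | 4-5% |
| 1 of 12 | 0.1% | 2% | 4-5% |
| 2 of 12 | 0.2% | 6% | 7% |
| 3 of 12 | 5% | 24% | 13% |

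I used the rank-sum test for the last column because the signed rank test named in the plan is for paired data and the comparison is between independent arms.

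**4. Dependence on the size of the rise.** On raw change, with equal shifts measured in SDs of change (harmless product 5%):
- 1 of 12: 3.8% at 5 SD, 0.8% at 10 SD, 0 from 20 SD.
- 2 of 12: 8.6% at 5 SD, 3.4% at 10 SD, 0.1% at 20 SD.
- 3 of 12: 22% at 5 SD, 23% at 10 SD, 14% at 20 SD, 6.8% at 30 SD, 0.8% at 50 SD.

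**5. Does counting recover significance?** Fisher's exact test for k/12 v 0/12 gives p = 1.00, 0.48, 0.22, 0.093 and 0.037 for k = 1 to 5. Newcombe's 95% interval for 3/12 v 0/12 uses Wilson limits of 0.089 to 0.532 and 0 to 0.243. Its lower limit is 0.25 − √(0.161² + 0.243²) = −0.04 and its upper limit is 0.25 + (0.532 − 0.25) = 0.53.

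**The case against.** A reader might infer from the limiting values that the primary test cannot reach significance with 1 to 3 of 12 injured, and that it flags such a product less often than a harmless one. The documents do not support that.
- The values in step 2 are a limit for very large rises on untransformed change. With 3 of 12 affected, the raw test rejects more often than 5% for shifts up to at least 30 SD, if severity is equal across those affected.
- The plan's skew rule would nearly always move the analysis off the raw scale in this scenario: a skewness test on pooled raw change was significant in over 99.9% of simulated trials. With 3 of 12 affected, the log and rank analyses reject in 24% and 13% of trials, both above the null rate.

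Three further arguments deserve weight. Counting does no better by the criterion of significance (step 5), so the shortfall is mainly the small sample. Affected participants would be seen anyway: *Objectives {7}* promises the frequency of new-onset laboratory abnormalities, *Criteria for discontinuing* has withdrawal and suspension rules, *Oversight and monitoring* provides DSMB review, and adverse events are compared between groups. Finally, the *Discussion* describes a composite judgement of safety, and nothing says that a non-significant mean change alone will establish it.

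All of this stands. It limits the harm but leaves the mismatch in place. The metric labelled primary is still not the one that was hypothesised or powered, and the count comparison is secondary in status and split by time point.

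**Conclusion.** The point holds as a mismatch and an insensitivity. The stated 80% power applies to a proportion and not to the primary laboratory metric. Under the ALT assumptions with an 8-fold rise in 1 to 3 of 12, the primary test rejects in roughly 0-24% of trials, depending on the number affected and the scale used. With a quarter of the arm affected, it misses the injury in at least about three trials of four on every permitted scale.

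The percentages rest on assumed SDs, on one analyte, and on every affected participant having a week 8 value in the per-protocol set. I made no calculation for creatinine or haemoglobin. The mismatch itself rests only on the text. This should be corrected, but it does not leave the trial without safety information.

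**What to change.** Make the primary laboratory outcome participant-level, as *Hypotheses* and *Sample size {14}* already frame it. This could be any new on-study abnormality, or each participant's worst on-study value in the harmful direction relative to their own baseline, taken across all visits and defined in advance. List affected participants, and report counts by arm with an exact or Newcombe 95% CI for the difference. Since the sizing endpoint also counts adverse events, state whether the 80% refers to that composite or to its laboratory part, and what control rate it assumes.

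Keep mean change at week 8 as a supportive analysis for small uniform shifts, and state that a non-significant result there does not by itself support safety. Say plainly that the count has little formal power at this size: 3/12 v 0/12 gives p = 0.22 and an interval of about −4 to 53 percentage points. The gain is alignment with the hypothesis and sizing, and open reporting with its uncertainty.

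The cost is revised wording and one variable derived from data already collected every 2 weeks. The existing Fisher comparison by time point can stay. The small downside is that a modest shift common to all participants becomes a supportive result.
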